#### CVD risk, CVD events and CVD death

CVD risk via FMH scores, blood pressure, heart rate and BMI will be compared between those successfully giving up smoking and continuous smokers by adjusting covariates. Moreover, the time event analysis approach will be applied to compare the CVD events and CVD deaths between the two intervention arms. Those outcomes will then be analyzed among the three arms of the study by applying the Cox regression model.

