### Study objectives

The primary objective is to compare the smoking cessation rate between a new evidence-based smoking cessation service package and the conventional 5 A approach to smoking cessation at the 1-year follow-up.

 The secondary objectives are:

1. to compare the smoking cessation rate at the 6-month follow-up.

2. to compare the CVD risk by Framingham general cardiovascular risk score among intervention and control groups at the 1-year follow-up.

3. to determine the characteristics of those who have successfully given up smoking and the determinants of behavioral change.

4. to determine the characteristics of relapse smokers after 6 months of cessation and the determinants of behavioral change.

5. to compare the cardiovascular disease events between ex-smokers, reduced smokers and continuous smokers at the 1-year follow-up.

6. to determine the cost-effectiveness of the new smoking cessation service package.

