#### Secondary outcomes

Secondary outcomes of the trial are:

1. Smoking cessation rate at the 6-month follow-up, proven by measurement of (ppmCO).

2. CVD risk measured by the Framingham general cardiovascular risk score at the 12-month follow-up.

3. Blood pressure and heart rate measured at the 6- and 12-month follow-up.

4. Number of CVD events and deaths at the 12-month follow-up.

5. Cost-effectiveness of the health service packages at the 12-month follow-up.

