#### CVD risk assessment

The CVD risk assessment will apply the general Framingham general CVD risk profile for primary healthcare [23,24]. Calculation of the Framingham CVD risk (FMH) score requires information relating to age, sex, blood pressure, diabetes status, smoking status and BMI. The FMH score will be assessed at the baseline, 6- and 12-month visits.

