### Analyses plan

All analyses for pre-specified outcomes in the trial protocol will strictly follow the intention-to-treat principle [33]. Statistical significance in all statistical analysis will be taken as a *P* value less than 0.05 with a 95% confidence interval. Relative risk (RR) for achieving primary outcome, smokerlyzer-confirmed smoking cessation, will be reported with the 95% confidence interval. Moreover, the number needed to treat (NNT) for achieving smokerlyzer-confirmed smoking cessation by the two intervention arms will be reported [34]. To overcome the contamination of the intervention, complier average causal effect (CACE) analysis will necessarily be applied.

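### The only comparison stated for Framingham score, blood pressure and heart rate is quitters versus continuing smokers, which conflicts with objective 2 for the score and with the intention-to-treat rule for all three

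*Protocol article*

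**What the plan says.** Four parts of the protocol article bear on this.

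- **Study objectives.** Secondary objective 2 is "to compare the CVD risk by Framingham general cardiovascular risk score among intervention and control groups at the 1-year follow-up".
- **Secondary outcomes.** Outcome 2 is "CVD risk measured by the Framingham general cardiovascular risk score at the 12-month follow-up" and outcome 3 is "Blood pressure and heart rate measured at the 6- and 12-month follow-up". BMI is not in the list.
- **Analyses plan.** The opening rule is "All analyses for pre-specified outcomes in the trial protocol will strictly follow the intention-to-treat principle".
- **CVD risk, CVD events and CVD death.** The contrast given is "CVD risk via FMH scores, blood pressure, heart rate and BMI will be compared between those successfully giving up smoking and continuous smokers", with adjustment for covariates. The next sentence changes the grouping: "the time event analysis approach will be applied to compare the CVD events and CVD deaths between the two intervention arms". The last sentence extends the analysis to all three arms by Cox regression.

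Under CVD risk assessment, the article says that the Framingham score "requires information relating to age, sex, blood pressure, diabetes status, smoking status and BMI".

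**The concern.** Whether a participant quits is decided after randomization and is the trial's primary outcome. People who quit are likely to differ from those who do not in motivation, dependence and family support, all of which the article itself names as influences on quitting. A comparison of the two groups is therefore observational, and covariate adjustment does not restore what randomization provides.

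For the Framingham score there is a second difficulty. A participant who quits is re-scored as a non-smoker, so the score falls even if nothing else about that person has changed. The grouping variable is built into the outcome.

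If the plan is carried out as worded, objective 2 is paired with an analysis that cannot answer it. Secondary outcomes 2 and 3 would then be reported on a contrast that does not estimate the effect of the service package. A reader could take a partly built-in difference in the score as evidence that the package lowers cardiovascular risk.

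**Working it through.** **1. Sections side by side.** The article states no figure to reproduce here, so the first check is of the text.

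| Measure | Listed outcome? | Grouping in objective 2 | Grouping in the analysis section | Conflict |
|---|---|---|---|---|
| Framingham score | Yes (outcome 2) | Randomized groups | Quitters vs continuing smokers | Objective 2 and intention-to-treat |
| Blood pressure, heart rate | Yes (outcome 3) | Not covered | Quitters vs continuing smokers | Intention-to-treat |
| BMI | No | Not covered | Quitters vs continuing smokers | None; observational only |
| CVD events and deaths | Yes (outcome 4) | Not covered | Randomized arms | None |

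The three-arm sentence specifies Cox regression, a method for event times, so it refers to events and deaths and does not supply a by-arm comparison of the score, blood pressure or heart rate.

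**2. Who would be compared.** Inputs from the Sample size section: 164 per arm; quitting 24% (new package) and 9% (routine).

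- Quitters: 164 × 0.24 = 39.4 and 164 × 0.09 = 14.8, total about 54.
- Continuing smokers: 328 − 54.1 = 273.9, about 274 (about 125 new package, 149 routine).
- Share from the new-package arm: 39.4/54.1 = 73% of quitters and 124.6/273.9 = 45.5% of continuing smokers.

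Each group mixes both arms, so the stated contrast is not the randomized one under another name. The count uses randomized participants only and ignores loss to follow-up.

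**3. The built-in part of the Framingham contrast.** The documents give no weight for smoking in the score. Assume that being a smoker multiplies the predicted risk by k, with k from 1.5 to 2.0, that all other inputs are equal, and that nothing else changes. Set a continuing smoker's score to 1.

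- Quitter vs continuing smoker: 1/k − 1.
- New package vs routine arm: (0.24/k + 0.76)/(0.09/k + 0.91) − 1.

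| k | Quitter vs continuing smoker | Arm means | New package vs routine |
|---|---|---|---|
| 1.5 | 1/1.5 − 1 = −33% | 0.92 and 0.97 | 0.92/0.97 − 1 = −5.2% |
| 2.0 | 1/2.0 − 1 = −50% | 0.88 and 0.955 | 0.88/0.955 − 1 = −7.9% |

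**4. How to read the gap.** The two contrasts differ by a factor of 33.3/5.15 = 6.5 at k = 1.5 and 50/7.85 = 6.4 at k = 2.0. Both are close to 1/(0.24 − 0.09) = 6.7, the dilution expected when an effect of quitting is spread over whole arms whose quit rates differ by 15 points. A fully genuine effect of quitting would show nearly the same ratio. It separates two estimands and is not a measure of bias.

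**5. What adjustment can do.** Adjusting for covariates cannot remove a term that is part of the outcome. Adjusting for the other inputs to the score would leave mainly the smoking term.

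**The case against.** The strongest reply is that the article never says the quitter contrast replaces the by-arm comparison. It is a condensed article and the statistical analysis plan is not shown. The by-arm comparison is in objective 2, intention-to-treat is declared for all pre-specified outcomes, and the baseline section gives the effect of cessation on cardiovascular risk as a purpose of the trial. The contrast could be an addition that serves this purpose. That has weight: a reader might infer that no randomized analysis of these outcomes will ever be done, and the article does not show that. What it does show is a named contrast that does not match the objective, next to a sentence that names arms for events and deaths only. That is a conflict in stated text and more than a detail left for later.

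Four further inferences are tempting and are not supported.

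- **That the quitter contrast is bound to give a significant benefit.** The built-in shift holds with other inputs equal. Quitters and continuing smokers are self-selected and may differ in blood pressure, BMI or age in either direction.
- **That the cost-effectiveness projections inherit the wrong contrast.** The Cost-effectiveness analysis section makes the Framingham-based projections between the arms.
- **That all four variables share every fault.** Circularity and the conflict with objective 2 concern the Framingham score only, and BMI is not a listed outcome.
- **That a by-arm Framingham comparison is free of the smoking term.** In the illustration, the whole 5% to 8% comes from it.

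**Conclusion.** The point holds in a limited form. For the Framingham score, the stated contrast conflicts with objective 2 and with the intention-to-treat rule, and it is partly circular. For blood pressure and heart rate, it conflicts with the intention-to-treat rule and is confounded but not circular. For BMI, it is an observational comparison that contradicts nothing.

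The textual conflict needs no numerical assumption. The sizes do: 33% to 50% between quitters and continuing smokers, and about 5% to 8% between arms, rest on an assumed smoking multiplier of 1.5 to 2.0, equal other inputs and the planned quit rates. They show direction and scale only.

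This should be fixed, but it does not threaten the main result. The primary outcome is compared between the randomized arms by chi-square test and relative risk, and CVD events and deaths are also compared by arm.

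**What to change.** In the section on CVD risk, CVD events and CVD death:

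1. Compare the Framingham score at 12 months, and blood pressure and heart rate at 6 and 12 months, between the two randomized arms under intention-to-treat, adjusted for the baseline value and for primary care unit, which is the randomization stratum.
2. Add a supportive by-arm analysis of the Framingham score with the smoking term held at its baseline value. As all participants enter as current smokers, this scores everyone as a smoker and shows change in the other components.
3. Keep quitters versus continuing smokers as a labelled exploratory analysis. Either omit the Framingham score from it or compute the score with smoking status held fixed.

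The cost is a change of wording. The article already plans the score at baseline, 6 and 12 months and blood pressure at those visits. Heart rate is in the baseline survey and is a listed outcome at 6 and 12 months. No new data or participants are needed.

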#### A path model of smoking cessation behavioral change

The structure equation model will be used to determine the factors influencing the behavioral change of patients at risk of CVD to stop smoking (Figure 3). Individual factors, such as age, sex, motivation to stop smoking and health literacy; social factors, such as perceived family support, income, household smoking prevalence and residence address; health service factors, such as medications and NRT use; tobacco-related factors, such as the number of cigarettes smoked, tobacco cost and cigarette type; and disease conditions, such as hypertension, BMI, diabetes and CVD risk on smoking cessation, will be analyzed using a holistic approach.

**Figure 3 F3:**
[figure not shown]
A path model of the smoking cessation behavior change hypothesis.

#### Cost-effectiveness analysis

The cost of interventions will be compared in terms of outcome achievement. The additional cost of producing an additional percentage of successful quitters at 1-year follow-up will be calculated. Based on the Framingham general cardiovascular risk score, differences in CVD events and deaths and the associated costs between the arms will be estimated for a period of 10 years at the end of the 1-year follow-up. Lifetime costs and health outcomes for our study population (aged 35 years and above) will be estimated using data both in and outside Thailand. Outcomes of the analysis will be: CVD events and deaths averted and cost over 10 years; incremental cost-effectiveness ratio (ICER) per CVD death averted; lifetime costs and quality-adjusted life years (QALYs) gained; and ICER per QALYs gained. The analysis will be performed using both the provider and societal perspective. All the future costs and outcomes will be discounted at a rate of 3% per annum. Sensitivity analysis will be employed to check the robustness of the results.

#### Qualitative analysis

The characteristics of a participant successfully giving up smoking will be analyzed qualitatively as a positive deviance.

## Discussion

Smoking cessation is considered to be the most urgent and high-priority intervention for prevention of non-communicable disease crisis internationally [1]. WHO estimated that 17.3 million people die of CVDs each year, 80% of which take place in low- and middle-income countries [4,10]. CVDs are preventable, and a substantial number of CVD-related deaths can be prevented by smoking cessation. Thailand, a middle-income country, is witnessing a rise in smoking prevalence, especially among the male population, with significant health and economic impacts [5,35,36]. Therefore, despite the nationwide controls on tobacco, strengthening the smoking cessation health service is an urgent necessity in Thailand [35]. The ESCAPE study aims to fill this gap by devising a multicomponent smoking-cessation service applicable at the primary care level.

In considering the individualized needs of patients in their attempts to give up smoking, a care approach package has been designed, the steps of which are outlined in Figure 4.

**Figure 4 F4:**
[figure not shown]
A conceptual model of evidence-based interventions and their actions in the development of behavioral change to stop smoking.

Existing evidence shows that interventions focusing on the motivation to give up smoking, such as motivational interviewing or brief counseling, can increase the rate of smoking cessation [37]. Having generated initial motivation to give up smoking, the challenge, in practice, is to sustain this motivation [27,38] (Figure 4). Evidence consistently states that the persistent offering of assistance, medication or behavioral support with the aim of smoking cessation is more effective than brief advice or a single session of counseling [38]. Recently, the sustainable impact of the nurse’s or allied healthcare worker’s empirical assertive approach was reported to have had a positive effect on cardiovascular risk factors, including smoking cessation [16]. Hence, this approach will be used in the current study for the new service arm.

Nursing interventions increase the smoking cessation rate, but the monitoring of smoking behavior remains a challenge [37]. In this study, PCU nurses will use smokerlyzers in the new service arm to monitor smokers’ attempts to give up smoking. Breath analysis results will be shown to participants, enabling them to see the decline in the CO level of their expired air.

Pharmacological interventions, such as nicotine replacement therapy (NRT), have been shown to work effectively within developed settings [39]. NRT relieves nicotine withdrawal symptoms and thus helps to sustain motivation to stop smoking [40]. However, in the developing setting of Thailand, while NRT has passed safety tests [41], the medication is not yet available via the publically financed health service system. Moreover, recent studies in Thailand heterogeneously reported that smokers and healthcare providers resorted to locally available herbs and remedies to relieve nicotine withdrawal and tobacco craving symptoms [12,42]. Thus, another challenge in designing an effective smoking cessation service is to provide free medication at the primary health care level to relieve nicotine withdrawal symptoms. Nicotine replacement chewing gum, therefore, will be included as one of the components in the new intervention arm of the ESCAPE study. Its cost-effectiveness will be analyzed with a view to replication in similar developing country settings.

Next, the need for support and care may differ among smokers (Figure 4); some patients may need motivation, some may need relief from craving symptoms by nicotine replacement therapy, and some may need buddy support [38]. Close monitoring and the kind support provided by a family member help smokers to succeed in giving up smoking [38,43]. Moreover, public health intervention aiming at lifestyle changes needs to focus on individual as well as social and environmental influences. In consideration of this, a component will be added to the new service package, that of close monitoring and continual support of the smoker by a family member (or other assigned member) using a sticker record diary. Social support may empower the smoker in his/her attempts to give up, while relieving the stigma of smoking that may be experienced by other family members [43].

Existing evidence suggests that a smoking cessation service, delivered in combination with other health services, might be a more effective approach than the conventional delivery through tobacco clinics [44,45]. The ESCAPE study is strategically designed to improve access to a smoking cessation service within the community. In this study, NCD clinics, regularly attended by patients at risk of CVD, are chosen as the centers to provide the smoking cessation service. Thus, smokers attempting to stop smoking will have easy access to the health service within their community. Moreover, this approach is expected to strengthen the follow-up and minimize the dropout number of participants during the research.

In this study a smoking cessation intervention at the primary health care level in the setting of northern Thailand will be tested. The 5 A approach is currently adopted by many hospitals in Thailand to treat smokers. The existing systems used at the study sites and the human resources available were observed. Based on existing global evidence, a new smoking cessation intervention package has been designed to treat smokers at the primary health care level. Its efficacy will be assessed by outcomes of behavioral change and cardiovascular risk reduction, and the cost effectiveness of achieving those outcomes. It is expected to generate a culturally tailored, practically effective smoking cessation service replicable in other developing countries.

## Trial status

Recruiting.

## Abbreviations

RCT: Randomized controlled trial; MH: Maetha hospital; PCU: Primary health care unit; FMH score: General Framingham scoring; CVD: Cardiovascular disease; SEM: Structural equation modeling; ICER: Incremental cost-effectiveness ratio; QALY: Quality-adjusted life years.
